| Foci not established                | The site of infection could not be identified after thorough diagnostic evaluation.                             |

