| Congestive heart failure                                                                |                  |         |                   |         | 1.65 (1.07–2.54)   | 0.04    |
| Any tumour                                                                              |                  |         | 2.04 (0.99–4.20)  | 0.05    |                    |         |
| Diabetes mellitus without end-organ damage                                              |                  |         |                   |         | 2.14 (1.35–3.39)   | 0.001   |
| Diabetes mellitus with end – organ damage                                               |                  |         |                   |         | 3.63 (1.65–7.99)   | 0.0006  |
| Previous non-bacteraemic S. aureus infection in the last 12 weeks                |                  |         | 24.9 (8.02–77.60) | <0.0001 | 7.84 (3.31–18.01)  | <0.0001 |
| Nosocomial acquisition                                                                  |                  |         |                   |         | 11.59 (7.89–17.02) | <0.0001 |
| Infection related surgical wound                                                        | 0.42 (0.21–0.86) | 0.02    |                   |         |                    |         |
| Deep tissue infection or abscess at the time first positive blood culture was taken     |                  |         |                   |         | 0.35 (0.22–0.56)   | 0.001   |
| Pneumonia as main focus of infection at the time first positive blood culture was taken |                  |         |                   |         | 1.77 (1.01–3.10)   | 0.05    |
| Foci not established at the time first positive blood culture was taken                 |                  |         |                   |         | 5.21 (4.19–6.48)   | <0.0001 |
| Methicillin-resistant Staphylococcus aureus (MRSA)                               | 3.96 (2.13–7.39) | <0.0001 | 12.2 (6.53–22.90) | <0.0001 | 5.69 (2.85–11.36)  | <0.0001 |
| Oxygen saturation, room air, pulse oximetry (per percent point)                         |                  |         | 0.94 (0.91–0.97)  | 0.0008  | 0.97 (0.95–0.99)   | 0.04    |
| Neutrophils count (per 10  cells/ $\mu$ L)                                  | 1.03 (1.01–1.05) | 0.002   | 1.06 (1.04–1.08)  | <0.0001 |                    |         |

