| Laboratory analysis                                               |                    |                   |                    |        |
| Lowest O2 saturation in %, median (IQR)                                  | 94· (93–94)        | 95 (94–95)        | 94 (91–95)         | <0·001 |
| Highest FiO2 %, median (IQR)                                             | 25 (22–39)         | 27 (26–36)        | 29 (29–36)         | <0·001 |
|                                                                          |                    |                   |                    |        |
| Serum CRP closest to first positive blood culture (mg/L), median (IQR)   | 185·0 (94·0–257·0) | 78·0 (31·0–165·0) | 172·0 (74·7–274·0) | <0·001 |
| Serum Creatinine (mg/dL), median (IQR)                                   | 1·07 (0·79–1·74)   | 1·06 (0·73–2·02)  | 1·15 (0·75–2·05)   | 0·58   |
| Neutrophil Count ( $\times 10^3/\mu\text{L}$ ), median (IQR)             | 10·5 (7·0–14·0)    | 9·0 (6·5–12·0)    | 10·8 (7·5–13·5)    | <0·001 |
| Leukocytes Count ( $\times 10^3/\mu\text{L}$ ), median (IQR)             | 12·7 (9·1–17·6)    | 10·0 (6·0–14·2)   | 12·0 (7·9–17·0)    | <0·001 |

 Retrospectively judgement, more than one allowed

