### Secondary Objectives

- 1 To evaluate the reproducibility of the clinical phenotypes and their correlation with mortality (30 days and 6 months).
- 2 To derive and validate a simplified probabilistic model of clinical phenotype assignment.
- 3 External validation of the simplified probabilistic model of clinical phenotype assignment in a prospective cohort and determination of associations with mortality and the development of complicated bacteremia within 6 months.
- 4 To apply microbiological (clonality testing, genome sequencing), biochemical and immunological techniques to elucidate the pathophysiological and genetic mechanisms underlying the phenotypes.

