## CRITICAL REVIEW OF THE LITERATURE.

*Staphylococcus aureus* is one of the main microorganisms that cause disease in humans and one of the main causes of bloodstream infections (bacteremia) worldwide. *S. aureus* bacteremia causes significant morbidity and increases healthcare costs; complications are frequent and mortality ranges from 20-40%. As a result, the concept of "complicated bacteremia" has been introduced. Predictors of complicated bacteremia are the persistence of bacteremia after 2-3 days of active treatment, the appearance of secondary foci of infection or infection of prosthetic valves and other prosthetic implants, endocarditis and specific cutaneous/mucosal lesions. More specifically, persistent bacteremia is considered a good predictor of possible complications and is a criterion for prolongation of antimicrobial treatment for 4 weeks. At the present time, the identification of

patients who develop complicated bacteremia is performed during the initial follow-up of the patient, pending the results of control blood cultures and other indicated diagnostic tests such as echocardiography. However, early identification of patients at high risk of developing complicated bacteremia would be of great use in planning treatment, monitoring for complications and evaluating more aggressive therapeutic strategies in this subgroup of patients. Independently of this, the pathogenesis of persistent bacteremia, when not due to endocarditis or an undrained focus, is not well established.

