### 4. Operational definitions of outcome, exposure and other variables.

- Outcome variables:
  - Primary outcome variable: all-cause mortality at day 30;

Secondary outcome variable: all-cause mortality at month 6 (measured as time-to-death, prospective cohort only). Persistent bacteremia (positive blood culture 2-3 days after initiation of appropriate targeted therapy). Complicated bacteremia (considered as presence of endocarditis, secondary foci, recurrence within 6 months). Hospital stay.

- 
- 

Explanatory: age, sex, service, type of acquisition (community-acquired, healthcare-related, nosocomial [Friedman criteria]; types of relationship with previous care), underlying diseases (diabetes, chronic lung disease, chronic renal insufficiency, chronic liver disease, immunosuppressive disorders, cancer, other), severity of underlying disease (Charlson index, McCabe classification), Barthel index, neutropenia, parenteral drug use, immunosuppressive treatment, recent invasive procedures (dialysis, catheter and vascular type, urinary catheter, mechanical ventilation, endoscopy, vascular procedures, surgery, percutaneous puncture), antibiotic therapy in the previous month, antibiotic susceptibility of *S. aureus*, Pitt and SOFA score on day 0 (blood cultures performed), sepsis or septic shock (Singer et al. JAMA 2016 for adults and Dellinger et al, Intensive Care Medicine 2013//Mathias et al, Curr Opin Pediatr 2016 for pediatric patients), acute kidney injury, empiric and targeted antibiotic therapy (drug, dose, route, day of onset and termination, reason for termination), source of bacteremia (clinical and microbiological criteria), management of source of infection (removal of catheter or other device, drainage), supportive care, echocardiographic data, if performed (transthoracic/transesophageal), CBC and basic blood chemistry at 0.

Exposure variables: Type of phenotype

- 

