## **8. Data analysis.**

ISAC Cohort: Objectives 1 and 2: Missing value analysis and imputation, if applicable, will be performed using standard techniques. To derive the phenotypes, a two-step cluster analysis with silhouette analysis will be performed on a randomly selected subcohort including two-thirds of the patients. The phenotypes will be represented as chord diagrams and heat maps. The distribution of phenotypes and characteristics will be validated on the other subcohort with one-third of the patients. Multivariate analysis (Cox or logistic regression) will be performed to control for the effects of antibiotic treatment and control of focus of infection on the association between the identified phenotypes and the outcome variable. Objective 3: A binary (if two phenotypes are obtained) or multinomial (if >2) logistic regression model will be used to predict the phenotypes obtained. A simplified probabilistic model of phenotype assignment will then be developed based on the final logistic regression model selected.

Prospective cohort: (Objective 4). Each patient with SAB will be assigned a phenotype that will be calculated on the basis of the simplified probabilistic model. Mortality rates (at 30 days and six months), persistent bacteremia and complicated bacteremia will be compared between the different types of phenotypes. Multivariate analyses (Cox or logistic regression) will be calculated to control for the effect of other covariates

(such as treatment administered or source control) on the association between identified phenotypes and outcome variables.

Study of genetic, immunological, biochemical and microbiological variables in representative patients with different phenotypes, randomly selected from the prospective cohort of HUVVM and HUVV cases (Objective 5):

Differences in frequencies or medians of the data for genetic virulence factors, biomarkers or immunological factors across the different phenotypes will be analyzed by the chi-square or Mann-Whitney U test and multivariate logistic regression models, taking into account possible confounding variables.

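### Complicated bacteraemia has no onset rule and no handling of death, so in phenotype C the planned comparison can make sub-phenotype C2 look protected

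*Combined protocol and SAP*

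**What the plan says.** **Outcome.** Methods Section 4 lists among the secondary outcomes "Complicated bacteremia (considered as presence of endocarditis, secondary foci, recurrence within 6 months". It gives no time origin, no new-onset requirement and no rule for foci found at day 0. The six-month window may attach only to recurrence.

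**Objective.** Secondary objective 3 (analysed under Objective 4 in Section 8) asks for "determination of associations with mortality and the development of complicated bacteremia within 6 months". The literature review is also closer to new events, since it speaks of "the appearance of secondary foci of infection or infection of prosthetic valves and other prosthetic implants".

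**Exposure.** Section 8 assigns each prospective patient a phenotype from the simplified probabilistic model. Table S6 gives the models for sub-phenotype 2, and the footnotes to Tables S10 and S11 say such models were used for assignment. One term in the C model is "Deep tissue infection or abscess at the time first positive blood culture was taken". Another is foci not established, with the same timing.

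**Analysis.** Section 8 states: "Mortality rates (at 30 days and six months), persistent bacteremia and complicated bacteremia will be compared between the different types of phenotypes". Adjusted analyses are to be Cox or logistic regression. No rule is given for patients who die without a complication, although the literature review says "complications are frequent and mortality ranges from 20-40" per cent.

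**The concern.** There are two separate problems, and within phenotype C they act in the same direction.

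First, if foci known at day 0 count as the outcome, a patient with a deep focus at the first culture is both less likely to be assigned to C2 and already an event. Part of the C2 v C1 association then follows from how the groups were formed and says nothing about what happens during follow-up.

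Second, a crude proportion or a logistic model treats death without a complication as a good result for this outcome. Sub-phenotype 2 has the higher mortality, so it has less time in which to show complications.

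Objective 3 is meant to show which patients go on to complications. Under either mechanism C2 could look protected, or a real excess in C2 could be hidden.

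**Working it through.** **1. Reproducing a printed figure.** Table S5, native heart valve: C1 47/403 = 11.7%, C2 35/694 = 5.0%. A two-sided Fisher exact test gives p = 0.00011, in agreement with the printed <0.001. The odds ratio C2 v C1 is (35/659)/(47/356) = 0.40 (95% CI 0.25 to 0.63). No event rate, sample size or power is stated for complicated bacteraemia, so there is nothing else of the plan's to reproduce.

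**2. Where the overlap is documented (Table S6).**

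| Model | Deep-focus term | Foci not established | Endocarditis term |
|---|---|---|---|
| A2 | none | none | none |
| B2 | none | none | none |
| C2 | deep tissue infection or abscess, aOR 0.35 (0.22 to 0.56) | aOR 5.21 (4.19 to 6.48) | none |

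The overlap is therefore shown for C only. C is the largest derivation group: 403 + 694 = 1,097 patients.

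**3. Illustration of the overlap.** Inputs are the native plus prosthetic valve rows of Table S5: C1 47 + 12 = 59, C2 35 + 15 = 50. Assumptions: no patient has both valve types, and all these foci were present at day 0 (Table S5 does not time them).

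- Prevalence p: 59/403 = 14.6% and 50/694 = 7.2%.
- With no new events, OR = (50/644)/(59/344) = 0.0776/0.1715 = 0.45.
- With an equal new-event risk r in both groups, total = p + (1 − p)r. At r = 10%: C1 0.146 + 0.854 × 0.10 = 0.232, C2 0.072 + 0.928 × 0.10 = 0.165, OR 0.65.
- At assumed r of 5%, 20% and 30% the OR is 0.58, 0.75 and 0.80.

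If only events after day 0 count and the true risks are equal, the OR is 1.00.

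**4. Illustration of death.** The 30-day death aHR for sub-phenotype 2 in C is 3.04 (1.84 to 5.02) in INSTINCT (Table S10) and 2.44 (1.47 to 4.06) in FEN-AUREUS (Table S11). Assumptions: these ratios hold to 180 days, the complication hazard is the same in both groups (20% risk absent death), and C1 mortality is 10% or 20%.

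With constant hazards, write c and d for the cumulative complication and death hazards. The cumulative incidence is c/(c + d) × [1 − exp(−(c + d))].

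- c = −ln(0.80) = 0.223.
- C1 at 20% mortality: d = 0.223, incidence 0.5 × (1 − 0.64) = 0.180.
- C2 at aHR 2.44: d = 0.544, incidence (0.223/0.768) × (1 − 0.464) = 0.156.
- OR seen by a logistic model: (0.156/0.844)/(0.180/0.820) = 0.84.

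| C1 mortality (assumed) | Death HR | OR, constant hazards | OR, all deaths in first 30 days |
|---|---|---|---|
| 10% | 2.44 | 0.92 | 0.85 |
| 10% | 3.04 | 0.89 | 0.79 |
| 20% | 2.44 | 0.84 | 0.72 |
| 20% | 3.04 | 0.79 | 0.63 |

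A complication risk of 10% or 30% moves these by at most 0.02. A Cox model that censors at death returns a hazard ratio of 1.00 throughout. One minus Kaplan-Meier would show 20% in both groups, above the 18.0% and 15.6% that occur in the worked example.

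**5. Timing of foci not established.** Table S1 defines it by "The site of infection could not be identified after thorough diagnostic evaluation", whereas Table S6 uses it as a variable fixed at the first positive culture. These definitions differ. Table S8 shows similar tension for INSTINCT: its site heading refers to the first culture, but its footnote reads "Retrospectively judgement, more than one allowed".

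**The case against.** The strongest reply is that nothing in the plan says day-0 foci will be counted. The objective and design sections speak of development, and the literature review speaks of foci appearing, so new onset may well be what was meant. That stands as far as it goes: the definition is ambiguous, and it may not be mistaken. Two analysts could still follow Section 4 faithfully and count different events.

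It is also fair that the explanatory list in Section 4 is not a list of clustering inputs, that the main A/B/C split is by portal of entry, and that the clustering variables are not in these documents. The overlap claim is therefore confined to the C model.

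On death, Section 8 permits Cox regression, and censoring at death gives a valid cause-specific hazard ratio. The distortion concerns the crude and logistic routes, which Section 8 leaves open. Excluding deaths in the first 48 hours reduces the problem but does not remove later deaths.

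Finally, the literature review says complicated bacteraemia is recognised during initial follow-up, while echocardiography and control cultures are pending. A focus first identified after day 0 may have been there all along, and predicting such foci is useful. That also stands. A date rule sorts by diagnosis, not by biological onset, and should be described that way.

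**Conclusion.** The point holds for the C2 v C1 comparison of a secondary outcome. The definition does not separate foci known at day 0 from later ones, the C2 model contains two terms that describe such foci or their absence, and the permitted crude and logistic analyses ignore death. Both mechanisms push C2 towards apparent protection. Neither can be sized, because no complication rates are given; the odds ratios above are illustrations under stated assumptions.

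Four stronger readings are tempting, and the documents do not support them.

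- **A 3.5-fold gap in deep foci before follow-up.** The valve, epidural, vertebral, joint, other-bone and abscess rows of Table S5 sum to 305 in C1 and 152 in C2 (0.76 v 0.22 per patient). These are entries, with more than one allowed, so the share of patients is bounded only at 17.1 to 75.7% v 5.0 to 21.9%. The table gives no timing, and a main site is not necessarily a secondary focus.
- **A spurious risk ratio of 0.77 to 0.88 from 20% v 40% mortality.** That range describes *S. aureus* bacteraemia in general. It is not a contrast between phenotypes.
- **Patients who die before work-up drift into C2.** Table S6 times the variable at the first culture, the retrospective footnote belongs to INSTINCT, and both deaths within 48 hours and missing follow-up cultures are exclusions. What remains is the mismatch between Tables S1 and S6.
- **The same fault in persistent bacteraemia.** Every patient is bacteraemic at day 0 and that outcome is read 2 to 3 days into targeted therapy, so a rule of being free of it at day 0 cannot apply.

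**What to change.** 1. Record the date on which each focus was first identified.
2. For the objective 3 analysis, count endocarditis or secondary foci first identified after day 0, or recurrence. Report foci known at day 0 separately by phenotype. State that this sorts by date of diagnosis, not onset.
3. As a sensitivity analysis, reassign C1 and C2 without the focus terms, including foci not established, and repeat the comparison.
4. For complicated bacteraemia, replace the open choice of Cox or logistic regression with cause-specific Cox models plus Aalen-Johansen cumulative incidence, with death as the competing event.
5. Reconcile the timing of foci not established between Tables S1 and S6.

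The cost is a date per focus, if not already collected (the data collection sheet is not included in the protocol), and a short change to the analysis text. The downside is fewer counted complications and hence wider intervals. Reporting the day-0 foci alongside keeps that information available.

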## 5. Expected sample size and basis for determination.

For the retrospective study (objectives 1-3) based on the ISAC database: we estimate that we will be able to analyze at least 1,800 cases of SAB that meet the inclusion criteria. For objective 4: we estimate prospective inclusion of 1000 cases from the 14 participating centers during 34 months of follow-up.

For objective 5: we estimate that 3 or 4 phenotypes will be identified, and therefore that 100 patients/isolate will be sufficient to provide 25-33 patients per phenotype, which will allow a reasonable number of cases for comparison of microbiological, genetic, endothelial and immunological parameters.

## **6. Data collection methods (prospective cohort).**

Data will be collected by prospectively obtaining information from DIRAYA of SAB episodes detected by the microbiology service at each of the participating Andalusian centers. Access to the electronic database, as well as prospective data collection to complete the electronic database, will be direct, remote, and carried out centrally by the HUVIM investigation team in conjunction with the local teams at each center. Patients will also be followed up for 6 months afterwards by center investigators.

Data will be collected in an eDCN (electronic data collection notebook) developed for the purpose:

### eDCN

A specific eDCN will be developed for this study. Based on experience with previous projects in SAB and using a tool developed by REIPI investigators that has already been registered, validated, and successfully tested in previous studies such as the FOREST, SIMPLIFY and PROBAC studies, a DCN will be designed that is intuitive for the user and clear and easy to analyze. Access to the eDCN will likely be through staff passwords only. Secure systems are used to ensure confidentiality, integrity and security. All data in the eDCN will be anonymized.

### Sampling

The study of genetic, immunological, biochemical and microbiological variables in representative patients with the different phenotypes will be performed only at the following centers: HUVIM and HUVV. Samples obtained during routine patient care will be used and no additional samples will be taken. All participants in this substudy will be informed and specific written informed consent will be obtained.

### Data sharing / Ethical issues

In accordance with current recommendations for data sharing, data from this study will be available to other investigators for meta-analysis following a written proposal, approval by the Ethics Committee and the PI of the study and the sponsor, and signing of an agreement with the PI and sponsor (FISEVI).

This is an observational study in which the main study variable is the identification of clinical phenotypes, with the application of microbiological (clonality testing, genome sequencing) biochemical and immunological techniques to elucidate the physiopathological and genetic mechanisms underlying the phenotypes. Hence, the study carries no risk for patients, since it does not involve any intervention or any additional or different treatment to that which patients would receive if they did not participate in the study. As indicated above, it is not considered an observational study with medicines according to the stipulations of Royal Decree 957/2020,

which regulates observational studies with medicines for human use. There will be no financial benefit for patients if they participate in the study. The data relating to the prospective cohort will be collected in a research file (electronic DCN) for which the Fundación Pública Andaluza para la Gestión de la Investigación en Salud de Sevilla (FISEVI) is responsible and which will adopt the appropriate measures to ensure the protection of data privacy.

The protocol developed as a result of this Project proposal will be evaluated by the CEIm for Andalusia.

This protocol will comply with the principles of the Declaration of Helsinki for research projects involving human subjects.

All personal data necessary for the development of the study will be collected and processed in accordance with the provisions of Regulation (EU) 2016/679 of the European Parliament and of the Council of 27 April 2016 on the protection of natural persons with regard to the processing of personal data and on the free movement of such data, and repealing Directive 95/46/EC (General Data Protection Regulation), with current Spanish legislation on data protection, and Article 16. 3 of Law 41/2002, of November 14, 2002, which regulates patient autonomy and the rights and obligations regarding clinical information and documentation.

